#### Short-term VR intervention trial

2.9.1

The DSST and BDS tests have been widely used in the field of VR environments for cognitive function, and they are highly responsive to the immediate effects of short-term interventions (Liu et al., 2022; Yin et al., 2018). Therefore, cognitive function is assessed by DSST (score range: 0–90) and BDS (score range: 0–9) scales. The DSST test is a simple and fast assessment tool that measures the ability to link symbols with numbers in 90 s (Beres and Baron, 1981). The DSST score is the number of symbols correctly filled in consecutively within 90 s. In the BDS scale, testing begins with three-digit numbers, which are read aloud to the participant, who is then required to repeat them in reverse. The test progresses sequentially to nine-digit numbers, with each sequence allowing up to two attempts. If a participant fails to correctly repeat a sequence of a specified length twice consecutively, the test is stopped. The number of digits in the longest correctly repeated sequence serves as the measure of cognition.

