#### Short-term VR intervention trial

2.11.1

The randomized block analysis of the variance module of PASS 11.0 was used to calculate the sample size. According to previous literature (Liao et al., 2020), the MoCA scores would increase by 0.5 points, and the Chinese version of the Verbal Learning Test (CVVLT) immediate recall scores would increase by 1.0 point after VR intervention. The DSST has been found to be more sensitive than the MoCA and CVVLT. Thus, we conservatively assumed that the mean difference in DSST scores between the intervention and control groups would be 1.0, with a standard deviation of 1.2. The number of blocks was set at 8, the significance level was set at *p* < 0.05 and the statistical power was set at 90%. Based on the above parameters, the minimum sample size per block is six individuals. Considering the possibility of noncompliance or refusal to participate, the sample size was increased by 20%, resulting in eight individuals per block. Thus, there are eight blocks in the short-term trial, with each block containing eight individuals.

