#### Short-term VR intervention trial

2.12.1

The analysis will be carried out according to the intention-to-treat principle. Given the short duration of this trial, missing data is expected to be minimal. Therefore, a single imputation will be used to process the incomplete data. Outliers will be identified using the interquartile range (IQR) method, defined as values below Q1 − (1.5 × IQR) or above Q3 + (1.5 × IQR), and will be replaced with Q1 − (1.5 × IQR) and Q3 + (1.5 × IQR), respectively. One-way analysis of variance (ANOVA) (for continuous and normally distributed variables) and chi-square test (for categorical variables) will be conducted to assess the baseline equivalence between the eight groups. If there are differences in characteristics between groups at baseline, the differences will be adjusted by performing multiple linear regression. ANOVA will be used to compare whether there are statistically significant differences in cognitive scores, heart rate and blood pressure among the eight groups. For each group, paired *t*-tests will be conducted to examine whether changes in cognitive scores, heart rate, and blood pressure are statistically significant between baseline, pre-intervention, and post-intervention. The identification of optimal biophilic elements will follow a two-stage analytic protocol. First, multiple linear regression models adjusted for covariates will be fitted to compare post-VR intervention cognitive scores between each intervention group and the control. Groups achieving a covariate-adjusted *p* < 0.1 in these pairwise comparisons will be considered statistically promising. Subsequently, among these candidate groups, the intervention demonstrating the largest adjusted mean difference in cognitive scores relative to the control group will be selected for long-term real environment intervention. Multiple linear regression will be used to evaluate the cognitive improvement in each group after adjusting for covariates. Continuous variables will be assessed for normality prior to analysis. If the data are not normally distributed, the Kruskal-Wallis H test will be used to compare the differences between the eight groups.

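### A normality check switches the eight-group comparison to Kruskal-Wallis; the switch itself costs little, but neither test uses the pre-intervention score, and one prespecified linear model should replace both

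*Protocol article*

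**What the plan says.** All analysis rules are in section 2.12.1 of the protocol article.

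- **Eight-group comparison:** "ANOVA will be used to compare whether there are statistically significant differences in cognitive scores, heart rate and blood pressure among the eight groups". No covariate is attached to this test.
- **Preliminary check:** "Continuous variables will be assessed for normality prior to analysis".
- **Consequence of failing it:** "If the data are not normally distributed, the Kruskal-Wallis H test will be used to compare the differences between the eight groups".
- **Scene selection, stated separately:** "multiple linear regression models adjusted for covariates will be fitted to compare post-VR intervention cognitive scores between each intervention group and the control". Then: "Groups achieving a covariate-adjusted *p* < 0.1 in these pairwise comparisons will be considered statistically promising". Among those groups, the one with the largest adjusted mean difference goes forward to the long-term trial.

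Section 2.9.1 defines the BDS score: "The number of digits in the longest correctly repeated sequence serves as the measure of cognition". Testing runs from three to nine digits. DSST is a count of symbols on a 0–90 scale. Section 2.5.1 has both tests given at baseline, after the stress phase (before the scene) and after the scene, so a pre-intervention score is already collected for each participant.

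**The concern.** The outcome data choose their own test. That is poor practice in general, and it works badly with these two outcomes. BDS is so coarse that a normality test on raw scores mainly detects that it is discrete, which says little about whether an F-test on group means is trustworthy. With eight groups of eight, DSST can fail by chance alone if each group is tested.

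Two things follow. First, the plan is inconsistent about BDS: the same scores could be judged unfit for ANOVA and then analysed by linear regression to choose the scene. Second, on both branches the eight-group comparison ignores the pre-intervention score. With eight participants per group, that score is the most obvious source of precision the trial has.

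**Working it through.** **Inputs from the documents.** Eight groups of eight, 64 in all; two-sided 0.05. Section 2.11.1 assumes "the mean difference in DSST scores between the intervention and control groups would be 1.0, with a standard deviation of 1.2".

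**Inputs assumed.** Shapiro-Wilk at 5% as the check; BDS as rounded normal values with mean 4–5 and SD 1–1.5; correlation ρ of 0.5–0.8 between pre- and post-intervention scores; 1.2 taken as the SD of the post-intervention score. The documents give none of these.

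**The plan's own figure.** Section 2.11.1 gives six per block for 90% power, raised to eight for 20% loss. The step from six to eight reproduces (6/0.8 = 7.5, rounded up to 8). The six does not: with six per group, a randomised-block ANOVA has 19% power if control differs from all seven scenes by 1.0, and 43% if four groups differ from the other four by 1.0. The article does not give the full pattern of means that was entered, so this is a separate matter. The calculations below use eight per group.

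**How often the check fails.**

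| Data | Each group tested | Pooled 64 | Residuals |
|---|---|---|---|
| DSST exactly normal | 1 − 0.95⁸ = 33.7% | 5.6% | 4.6% |
| DSST whole numbers, SD 10 (assumed) | 36% | 5% | 5% |
| DSST whole numbers, SD 1.2 | 92% | 100% | 14% |
| BDS | 78–100% | 95–100% | 7–97% |

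The BDS ranges span several sets of simulations. A separate set put raw-score failure at 83–100%.

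**Power of the eight-group test.** Take control at 0 and all seven scenes at +1.0. The squared deviations of the eight means sum to 7/8 = 0.875.

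- *Stated ANOVA:* noncentrality λ = 8 × 0.875 / 1.2² = 7/1.44 = 4.86. On 7 and 56 degrees of freedom the power is 27% (simulated 26–28%).
- *Kruskal-Wallis:* simulated 20–22%, so about 5–7 points lower.
- *Normal DSST, per-group check, then ANOVA or Kruskal-Wallis:* 24–27%, so 1–2 points lower on average, because the check fires in only about a third of trials.
- *Linear model with the pre-intervention score:* λ = 4.86/(1 − ρ²), on 7 and 55 degrees of freedom.

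| ρ | λ | Power | Simulated, no check | Simulated, per-group check in front |
|---|---|---|---|---|
| 0.5 | 6.48 | 36% | 34–37% | 29–32% |
| 0.7 | 9.53 | 53% | 52–53% | 42% |
| 0.8 | 13.5 | 71% | 70–71% | 54% |

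A check placed in front of the adjusted model therefore loses about 5 points at ρ = 0.5 and about 16 at ρ = 0.8.

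**Error rate.** With no true differences, separate simulations of the checked procedure (ANOVA or Kruskal-Wallis) gave rejection rates between about 4% and 5.5%, which is nominal within simulation error.

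**The case against.** The strongest reply is that the check does little harm, and much of that reply stands.

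- **A reader might infer that the check itself causes a large loss of power.** The documents do not support this. The test it displaces is the unadjusted ANOVA of section 2.12.1, and that swap costs about 5–7 points when it happens. The large gap is to a baseline-adjusted model that the plan does not name for this comparison, and plain ANOVA has nearly the same gap.
- **A reader might infer that the switch removes adjustment for the pre-intervention score.** The stated ANOVA has none to remove, and the article does not say that Kruskal-Wallis replaces the regressions described separately.
- **A reader might infer that the choice of scene is put at risk.** Selection rests on the adjusted regression. Nothing sends that regression through the check or makes it conditional on the eight-group test.
- **The failure rates depend on an unstated choice.** The article names no test, level or unit for the check, which could even be graphical. An analysis plan that is not shown may settle this, so the silence is not itself a fault. The wording does speak of checking variables before analysis, which points to raw scores rather than residuals. On raw scores, BDS fails in most or nearly all trials.

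What remains is that a data-driven choice of test is fixed for a primary outcome, that it fits BDS poorly, and that neither branch uses information already collected.

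**Conclusion.** The point holds in a limited form. The normality check is a poor rule for these outcomes, but it does not invalidate the analysis and its direct cost is small: 1–2 points on average for normal DSST, and about 5–7 points where it fires nearly always, as is likely for raw BDS. The gain worth having comes from replacing both tests with one adjusted model, which raises power for the eight-group comparison from about 27% to about 36–71%.

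That range rests on an assumed correlation of 0.5–0.8, on all seven scenes being better than control by 1.0, and on reading the stated 1.2 as the SD of the post-intervention score. If 1.2 already describes a change or a residual, the gain would be smaller. The inconsistency over BDS needs only that the check be made on raw scores. The scene selection is not directly affected.

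**What to change.** In section 2.12.1:

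1. Delete the normality check and the switch to Kruskal-Wallis.
2. For both DSST and BDS, make the eight-group comparison from one prespecified linear model of the post-intervention score on group and pre-intervention score, whatever the shape of the data. Use the same model and covariates for the scene-against-control comparisons that drive selection.
3. Keep Kruskal-Wallis as a sensitivity analysis.
4. If protection against non-normality at eight per group is wanted, take p-values by permutation within randomisation blocks. Permute all arms for the eight-group test, but only the labels of that scene and control for each scene-against-control test. Permuting all arms tests the hypothesis that no scene has any effect, and this is not automatically valid for one scene when others work. If every block has size 8, each such comparison has 2⁸ = 256 allocations, enough for a 0.1 threshold.

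The cost is a reworded paragraph and, if permutation is used, a short program. No visit, measurement or sample size changes.

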#### Long-term real environment intervention trial

2.12.2

The modified intention-to-treat population (mITT) will be used for statistical analysis. Missing values will be imputed using multiple imputation. Firstly, two sample t-tests (for continuous and normally distributed variables) and chi-square test (for categorical variables) will be conducted to assess the baseline equivalence between the intervention and control groups. Two sample t-tests will be used to compare whether cognitive scores are statistically different between two groups. Multiple linear regression will be used to demonstrate whether the intervention is statistically associated with cognitive scores after adjusting for potential confounders. Repeated measures ANOVA will be used to compare cognitive scores across groups. The potential confounders will be corrected in the mixed-effect model to determine the association between intervention and cognitive scores. If the intervention has a direct effect on cognitive function, longitudinal causal mediation analysis will be further used to clarify the mediating factors through which the intervention may affect cognition.

To explore the interaction of *APOE4* and the biophilic environment on cognition, we will perform stratified analysis according to groups to clarify the main effects of *APOE4* on cognitive function. Then, mixed models will be used to adjust for potential covariates and to elucidate the main effect of *APOE4* on cognitive function in each group. Finally, the interaction term between the *APOE4* and the intervention group will be included in the mixed-effects model to identify the effect of the genetic-environmental interaction on cognitive function.

In our study, all statistical tests are two-tailed, with a significance level of *p* < 0.05.

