Preparation Phase: first, researchers provide a concise introduction to the study procedures. Participants rest for 5 min, and heart rate and blood pressure are measured using an Omron medical electronic blood pressure monitor (HBP-1300). Then, baseline data are collected through a questionnaire survey. The structured questionnaire includes general demographic characteristics such as age, gender, height, weight, ethnicity, education level, marital status, and income. It also includes lifestyle behaviors such as smoking, alcohol consumption, and physical activity, medical histories such as hypertension, diabetes, and cardiovascular disease, and medication history. An assessment of mental health status is conducted using the Center for Epidemiologic Studies Depression Scale (10-item, CESD-10). Finally, cognitive scores are assessed using the Digit Symbol Substitution Test (DSST) and the Backward Digit Span (BDS) scale. After the measurements, researchers provide the VR headset to participants and allow them to adapt and learn basic operations for up to 5 min. All VR devices look the same shape and color.Stress Phase: participants are exposed to a cluttered living environment through VR, with background noise from bustling traffic and mechanical devices. Then they undergo stress-inducing tests, including a memory test and an arithmetic test. The stress phase lasts for 5 min. After this phase, cognitive scores (DSST/BDS), heart rate, and blood pressure are re-measured.VR Intervention Phase: participants will engage in a 10–15 min of VR scenario intervention according to their group allocation. Depending on their groups, some participants may simulate activities such as walking indoors, opening doors, pulling curtains, watering plants, or feeding fish. After completing the VR intervention, cognitive scores (DSST and BDS), heart rate, and blood pressure are measured again. Additionally, the Environmental Semantics Differential Scale (SD) and the Restoration Scale (RS) are also evaluated.

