**Figure 3 fig3:**
[figure not shown]
Long-term trial flow chart. MoCA, the Montreal Cognitive Assessment scale; DSST, the Digit Symbol Substitution Test; PSQI, the Pittsburgh Sleep Quality Index; GDS-15, 15-item Geriatric Depression Scale; FBG, fasting blood glucose; HbA1c, glycated hemoglobin; p-tau181, tau phosphorylated at threonine 181; esRAGE, endogenous secretory receptor for advanced glycation end-products; IL-6, interleukin-6; *APOE*, E4 variant of apolipoprotein E.

At baseline, after the participants sign the informed consent form, they will be administered a questionnaire to collect the following information: demographic characteristics (sex, date of birth, education), behavioral risk factors (dietary habits, smoking, alcohol consumption, physical activity, etc.), chronic disease history, medication history, the Lubben scale for social interaction, the Montreal Cognitive Assessment (MoCA) scale, DSST, the Pittsburgh Sleep Quality Index (PSQI), and the 15-item Geriatric Depression Scale (GDS-15). After completing the questionnaire, participants will undergo a physical examination (including blood pressure, heart rate, height, weight, and waist circumference), and then 2 mL blood samples will be collected by venipuncture. Then, researchers will distribute the wGT3x-BT accelerometer (Actigraph) to part of the participants. The wGT3x-BT accelerometer will objectively collect data regarding physical activity and sleep patterns, including time spent in light, moderate, and vigorous physical activity, sedentary time, sleep duration, and sleep efficiency. After completing the aforementioned steps, envelopes will be opened to decide which group the subjects would be enrolled in.

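### Neither trial guarantees adjustment for the pre-intervention cognitive score it collects, and the short-term trial ties adjustment to baseline significance tests

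*Protocol article*

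**What the plan says.** **Short-term trial, section 2.12.1.** Baseline tests "will be conducted to assess the baseline equivalence between the eight groups", and the text continues: "If there are differences in characteristics between groups at baseline, the differences will be adjusted by performing multiple linear regression". The group comparison is then: "ANOVA will be used to compare whether there are statistically significant differences in cognitive scores, heart rate and blood pressure among the eight groups". No covariate is attached to that ANOVA, nor to the Kruskal-Wallis fallback. The element that goes forward is chosen separately: "multiple linear regression models adjusted for covariates will be fitted to compare post-VR intervention cognitive scores between each intervention group and the control". The threshold is "Groups achieving a covariate-adjusted *p* < 0.1 in these pairwise comparisons will be considered statistically promising", followed by the largest adjusted difference. The covariates are not listed.

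**Short-term data, section 2.5.1.** DSST and BDS are taken at baseline and again between the stress phase and the VR scene: "After this phase, cognitive scores (DSST/BDS), heart rate, and blood pressure are re-measured". A pre-VR value of each test therefore exists for each participant who reaches the VR phase.

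**Long-term trial, section 2.12.2.** Four analyses of cognitive scores appear in sequence: "Two sample t-tests will be used to compare whether cognitive scores are statistically different between two groups"; a multiple regression and a mixed-effects model, each adjusted for confounders that are not named; and a repeated measures ANOVA. None is marked as the main one. Baseline equivalence is tested, but no rule makes adjustment depend on the result.

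**Long-term data, section 2.5.2.** The baseline questionnaire includes "the Montreal Cognitive Assessment (MoCA) scale, DSST". DSST is repeated at 12 and 24 months, and MoCA at 24 months.

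**The concern.** A person's earlier score on a test is usually among the best predictors of the later one. If it is left out, stable differences between people stay in the error term, and chance differences in starting level pass into the group comparison.

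A baseline significance test is a poor way to decide when to adjust. Under randomisation it can detect only chance, and its p-value says nothing about how strongly the variable predicts the outcome. With 8 per group it also misses large imbalances. The resulting model depends on the data.

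The short-term trial is where this matters most. Its adjusted differences decide which element the long-term intervention group lives with for 24 months. If the pre-VR score is not among the unnamed covariates, a lucky starting imbalance can influence that choice. In the long-term trial the stake is precision, and the freedom to choose among four unranked analyses.

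**Working it through.** **Inputs.**
- Section 2.11.1: DSST difference 1.0, SD 1.2; eight groups of 8 (64 in total).
- Section 2.12.1: selection threshold p < 0.1.
- Section 2.11.2: 120 per group with about 20% loss, so 120 × 0.8 = 96; 90% power, two-sided 0.05.
- Correlation r between the earlier and later score: not in the article; assumed 0.3 to 0.8.

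**The plan's own sample sizes.** These do not reproduce as individually randomised two-group comparisons. For the long-term trial, 2 × (0.017/0.02)² × (1.960 + 1.282)² ≈ 15.2, so 16 per group, against the stated 99. For the short-term trial, 2 × 1.2² × (1.960 + 1.282)² ≈ 30.3, so 31 per group, against the stated 6 per block. That is a separate matter. The long-term results below are therefore in SD units, and the short-term results use only the stated difference and SD.

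**1. Gain from always adjusting.** Relative to an unadjusted comparison of post scores, the variance factor is 1 − r².
- Short-term, one group against control: unadjusted SE = 1.2 × √(2/8) = 0.60, so the non-centrality is 1.0/0.60 = 1.67. Power uses the non-central t with pooled df 64 − 8 = 56, or 55 once the covariate is fitted. Adjustment multiplies the SE by √(1 − r²).
- Long-term: with 96 per group (df 190) the 90% detectable difference is 0.470 SD, multiplied by √(1 − r²).

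| r (assumed) | 1 − r² | Variance reduction | Short-term power, p < 0.1 | Long-term detectable difference |
|---|---|---|---|---|
| unadjusted | 1.00 | – | 0.50 | 0.47 SD |
| 0.3 | 0.91 | 9% | 0.53 | 0.45 SD |
| 0.5 | 0.75 | 25% | 0.60 | 0.41 SD |
| 0.7 | 0.51 | 49% | 0.75 | 0.34 SD |
| 0.8 | 0.36 | 64% | 0.86 | 0.28 SD |

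**2. Can the baseline test catch imbalance with 8 per group?** The SE of a baseline difference between two groups is √(2/8) = 0.5 SD, so about 32% of pairwise differences exceed 0.5 SD by chance (two-sided normal tail beyond 1 SE). If one group lies d SD away from the other seven, the eight-group F test has non-centrality 8 × d² × 7/8 on 7 and 56 df. For d = 0.5 this is 1.75 and the power is 0.12. For d = 1 it is 7.0 and the power is 0.39. Most such imbalances would go unadjusted.

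**3. What test-then-adjust recovers.** This was simulated with 2,000,000 draws per scenario for a two-group comparison with 90% power unadjusted, large-sample normal statistics, and the baseline score itself as the tested characteristic.

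| r | Power, test-then-adjust | Power, always adjust | Type I error, test-then-adjust |
|---|---|---|---|
| 0.5 | 0.910 | 0.963 | 0.043 |
| 0.7 | 0.917 | 0.995 | 0.036 |
| 0.8 | 0.920 | >0.999 | 0.030 |

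When the baseline difference falls just short of significance (z = 1.9), the unadjusted test that the rule then uses has conditional type I error 0.12, 0.19 and 0.23 for r = 0.5, 0.7 and 0.8. The rule gains little power and leaves the near-miss imbalances uncorrected. This illustrates the mechanism; it is not a simulation of the eight-group trial.

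**The case against.** Several stronger readings are tempting, and the article does not support them.

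- **That the long-term trial adjusts only after a significant baseline test.** Section 2.12.2 contains no such rule; its regression and mixed model adjust unconditionally. The trigger is stated only in section 2.12.1.
- **That the short-term selection is unadjusted.** The selection regression, its p-value and the difference it ranks on are all covariate-adjusted, with no baseline-test condition. The unadjusted power of 0.50 is therefore a reference point and does not describe that step. What stands is that the covariates are unnamed, so nothing guarantees that the pre-VR score is among them.
- **That the t-test or ANOVA is the primary analysis, on post-intervention scores.** No analysis is labelled primary, and neither sentence says whether the score is a post value or a change. Only the selection regression is explicitly on post-VR scores.
- **That repeated measures ANOVA dilutes the effect by averaging in the baseline visit.** This would hold only if the group main effect were the estimate, which the article does not say. A group-by-time term would not average in baseline; with two visits (MoCA) it equals a comparison of change scores. The repeated-measures and mixed models may therefore already use baseline as a repeated outcome and recover part of the gain.

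It can also be said that a journal article may leave its covariate list to the full plan, that an unadjusted comparison in a randomised trial is unbiased on average, and that r is assumed and need not be the same within one session and over 24 months. If 1.2 is the SD of a change score, much of the short-term gain is already in that figure. All of this limits the size of the point. It does not answer it: the adjustment trigger and the unadjusted tests are methods the article states, not details it omits.

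**Conclusion.** The point holds in limited form. The short-term trial states a significance-triggered adjustment rule and an unadjusted eight-group ANOVA, and its selection regression does not secure the pre-VR score as a covariate. The long-term trial lists four unranked analyses, one of them an unadjusted t-test, and fixes baseline DSST or MoCA as a covariate in none.

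The direction of the gain is the same across the assumed range of r, but its size is uncertain: between slight (9% less variance) and large (64%). The figures in the working are measured against an unadjusted post-score comparison, and the short-term ones also require 1.2 to be the SD of the post score. For the long-term trial this is a matter of efficiency and clarity, not of bias on average. It should be corrected, but it does not invalidate either trial.

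**What to change.** **Section 2.12.1.** Delete the sentence that makes adjustment depend on baseline differences; baseline characteristics can still be described. In both the eight-group comparison and the selection regression, always include the post-stress (pre-VR) score of the same test: DSST for DSST, BDS for BDS. The ANOVA then becomes an ANCOVA. Name any further covariates in advance.

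**Section 2.12.2.** For each cognitive score, name one ANCOVA or mixed model as the main analysis, with the baseline value of that score as a fixed covariate and the 24-month group difference as the estimate. For DSST the mixed model can take the 12- and 24-month values as outcomes; for MoCA, measured only at baseline and 24 months, an ANCOVA is enough. Describe the t-test, the other regression and the repeated measures ANOVA as supportive, or remove them.

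**Cost.** Changes to the analysis wording only. Every score needed is already scheduled, so no new data, visits or participants are required.
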